### Cognitive intervention

In the aspect of cognitive intervention, the China’s Cognitive Training Guideline indicates that cognitive training is suitable for cognitively normal older adults, those with subjective cognitive decline, mild cognitive impairment, and dementia patients. Cognitive training uses systematically designed tasks to target cognitive domains such as attention, memory, and logical reasoning, with adaptive difficulty levels to enhance individual cognitive function [29]. The recommended approach covers various cognitive domains, including but not limited to memory, attention, reasoning, and executive functions. The training dosage suggests a minimum of 30 min per session, at least three training sessions per week, with a total training duration of no less than 20 h to achieve significant effects, meaning continuous training for at least three months. Based on the framework provided by the guideline and practical content from previous studies [30–33], we outline attention training (e.g. Schulte grids, color-word training), memory training (e.g. picture memorization, recall training), logical reasoning (e.g. sudoku, matchstick training), and executive function training (e.g. finger exercises, building blocks) (Supplementary Table 1).

During each group intervention session, cognitive training will last for 60 min, covering 2 ∼ 3 training methods to ensure a balance between reinforcing existing knowledge and acquiring new training content. The primary objectives of the group intervention include enabling participants to master training methods in different cognitive domains for independent application during individual family intervention; teaching practical memory strategies to help participants better address daily challenges; and promoting participant engagement through face-to-face discussions and interactions while enhancing their sense of social involvement.

The cognitive training assignments for individual family intervention will include all the training content that has been taught. The assignments will be designed to meet the weekly training requirements of participants. Participants will record their individual family intervention training activities three times a week on the SilverHealth Pro Platform. Based on participants’ feedback on the difficulty and completion of training tasks, medical staff will make corresponding adjustments to the training content.

### Exercise intervention

According to the International Exercise Recommendations in Older Adults [5], older adults should engage in 150 min moderate-intensity aerobic exercise per week or 75 min vigorous-intensity aerobic exercise, along with muscle-strengthening exercises (resistance training) on ≥2 days. The Physical Activity Guidelines for Americans [34] recommends that the most suitable exercise regimen for older adults to maintain health is the multicomponent exercise, involving balance training, resistance training, and at least moderate-intensity aerobic exercise training ≥3 times a week, with each session lasting 30 ∼ 45 min. Therefore, we will adopt a multicomponent exercise training approach, including aerobic exercise, resistance training, balance, and flexibility training. The training objective is to combine group intervention with individual family intervention ≥3 times a week, with each session lasting ≥45 ∼ 60 min.

The group intervention for exercise training will last 45 min each time, incorporating resistance training, balance training, and flexibility training (Supplementary Table 2). As the group intervention progresses, we gradually introduce the use of resistance bands, dumbbells, and sandbags to increase difficulty in resistance movements, aiming for progressive resistance training. The group intervention helps participants grasp the key points of multicomponent exercises and provides training charts and videos for individual family interventions. Additionally, we will provide participants with a recommended list of aerobic exercises, allowing participants to autonomously choose suitable types of aerobic exercises for individual family interventions. Based on the participants’ completion of exercises during the group intervention and feedback on exercise training during individual family interventions, medical staff will provide personalized exercise recommendations.

We will require participants to exercise with support (such as a chair or railing) to ensure the safety of the exercise process. Intermittent rest breaks and hydration will be provided throughout the exercise session. Medical staff will inform participants that they may experience delayed onset muscle soreness as a normal response to exercise due to muscle adaptation. If participants feel pain or discomfort or are unable to tolerate the exercise, they will be advised to rest or adjust the intensity of the exercise.

### Nutritional intervention

Nutritional intervention consists of dietary guidance, nutritious meal demonstration, and nutrition lectures. Nutritional guidance has the advantages of being effective in intervention and highly operational, helping older adults to change their daily diets and establish healthy eating habits [35], thereby enhancing their nutritional literacy and improving their nutritional status [36].

Nutritionists will apply the Dietary Guidelines for Chinese [37] as a guiding basis and emphasize the importance of a balanced diet for older adults during the nutritional guidance process. The group intervention for nutritional guidance will last 15 min each session. The first two sessions will primarily introduce the dietary structure and guidelines for older populations, providing quantified charts of common foods to help participants understand the types and portions of food they should consume daily. The following eight sessions will be conducted in the form of themed lectures to guide older adults on healthy eating habits, with three nutrition meal demonstrations provided to assist participants in developing suitable dietary plans (Supplementary Table 3). Furthermore, common dietary questions from participants will be addressed one by one during every group intervention session.

Participants will be required to complete dietary logs three times a week for individual family interventions, recording the staple foods, protein sources, vegetables, fruits, lipids, etc., consumed during breakfast, lunch, and dinner in the form of pictures or text. Medical staff will evaluate the adequacy of the participants’ diets based on their individual nutritional status, provide feedback for improvement, and respond through the SilverHealth Pro Platform.

### Outcome measures

Trained data collectors will conduct questionnaires and physical examinations with the participants. Additionally, the participants will undergo blood tests and body composition analysis. Data will be collected at three different times: post-randomization baseline, 6-month, and 12-month timepoints. The flowchart of the study protocol is displayed in Figure 2. Data collectors and data entry personnel neither participate in the intervention nor are aware of the participants’ group assignments.

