### Randomization, blinding, and allocation concealment

Participants who meet the inclusion and exclusion criteria will be randomized into intervention and control groups in a 1:1 ratio. The randomization process will be carried out by a data custodian not involved in the study. The data custodian will generate a set of random numbers using a simple randomization procedure and place into sequentially numbered, sealed, opaque envelopes. The random numbers will be assigned to participants in numerical order. Participants in the intervention group will be informed about the intervention procedure and follow-up plan, while participants in the control group will be informed about the follow-up plan. If participants agree to their assigned plan, they will sign the informed consent and undergo further baseline assessment.

Due to the difficulty of blinding intervention implementers and participants in a multidomain intervention, data collection personnel and statistical analysts will be blinded to reduce bias. Participants are instructed not to disclose their group assignment to anyone during baseline and follow-up assessments.

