**Figure 2. F0002:**
[figure not shown]
Flow chart of multidomain intervention.

The primary outcomes are the change in epigenetic age acceleration and pace of aging. We will apply eight representative aging clocks in our primary outcomes: Horvath, Hannum, GrimAge, PhenoAge, DunedinPACE, GrimAge version 2, PC-PhenoAge, and PC-GrimAge. Epigenetic age acceleration is defined as the residuals of the linear regression of DNA methylation age on chronological age, which can be calculated by seven clocks (Horvath, Hannum, GrimAge, PhenoAge, GrimAge version 2, PC-PhenoAge, and PC-GrimAge). The rate of aging represented by DunedinPACE is also the primary outcome we are concerned about.

The secondary outcomes are the changes in frailty score and IC Z-score. Other outcomes include physical functions, body composition, aging biomarkers, inflammatory markers, haematology and biochemistry parameters, and lifestyle factors (Table 1).

**Table 1. t0001:** Overview of outcomes and assessment time points.

Outcomes	Outcome measures	Screening	Baseline	6 months	12 months
Primary outcomes					
Epigenetic age acceleration and pace of aging	Horvath, Hannum, GrimAge, PhenoAge, DunedinPACE, GrimAge version 2, PC-PhenoAge, and PC-GrimAge		√	√	√
Secondary outcomes					
Frailty	Fried phenotype	√	√	√	√
Intrinsic capacity	IC Z-score: cognition: MMSE; locomotion: SPPB; vitality: MNA; psychology: GDS-15	√	√	√	√
Other outcomes					
Physical functions	Handgrip strength	√	√	√	√
	Gait speed: 4-m walk test	√	√	√	√
	Timed up-and-go test	√	√	√	√
	Five-times sit-to-stand test	√	√	√	√
Body composition	BMI, waist-to-hip ratio, skeletal muscle mass, skeletal muscle index, body fat percentage, visceral fat area, phase angle	√	√	√	√
Aging biomarkers	Telomere length		√	√	√
	Mitochondrial DNA copy number		√	√	√
Inflammatory markers	hsCRP, homocysteine		√	√	√
	IL-1β, IL-2, IL-4, IL-6, IL-8, IL-10, IL-13, IFN-γ, TNF-α, MCP-1, Eotaxin, CXCL9, CXCL10, CX3CL1, sTNF-R1, sTNF-R2, G-CSF、GM-CSF, VEGF, RANTES, TRAIL		√	√	√
Haematology and biochemistry parameters	Hemoglobin, platelets, neutrophils, hematocrit, white blood cell count; blood urea nitrogen, creatinine, uric acid, glucose, albumin, total bilirubin, alkaline phosphatase, alanine transaminase (ALT), aspartate transaminase (AST), lipid profile		√	√	√
Lifestyle factors	Dietary diversity	√	√	√	√
	Physical activity and sedentary time	√	√	√	√
	Health literacy	√	√	√	√

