In this study, we chose epigenetic clocks as the primary outcome measures due to its well-established role as a biomarker of biological aging and its sensitivity to lifestyle interventions. Geriatricians can utilize the DNA methylation age to explore the underlying mechanisms of aging, investigate factors related to aging, and evaluate the effectiveness of aging interventions [68]. In addition, there are dedicated online platforms and open-source R packages for calculating the methylation age. This enables the use of methylation age as a biomarker for quantifying aging in different populations, and also makes the results of various studies comparable and generalizable. If this study is successfully implemented, it will provide valuable experiences and models for health management and aging intervention for older populations in other regions. With the context of an aging society, our findings may provide new insights for public health managers in promoting proactive health, which involves leveraging existing healthcare resources and community networks to enhance the health and well-being of older adults.

There are also inherent limitations to the study design. Participants and the intervention staff could not be blinded due to the nature of our intervention contents. We do not consider this to be a significant issue as we will employ blinding for outcome assessors and utilize a Zelen-design for randomized controlled trial which is more in line with clinical practice reality. Additionally, we plan to conduct one-to-many teaching operations in the group intervention rather than one-to-one due to manpower costs. While this may impact the intervention’s effectiveness, it is a common issue when generalizing intervention models to more community healthcare institutions with more participants. We need to explore the most cost-effective intervention strategy in future practice. Moreover, our study will exclude participants with moderate to severe cognitive dysfunction (MMSE score *≤* 20) to ensure ethical rigor and protocol compliance. Although this approach enhances the internal validity of our findings, it may limit the generalizability of the IC results to populations with cognitive impairment. Future studies should explore IC in individuals with cognitive dysfunction to provide a more comprehensive understanding of this construct.

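### The named baseline for frailty and intrinsic capacity is taken after participants know and accept their arm, although Table 1 also schedules a measurement before randomisation; text and table must be reconciled

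*Protocol article*

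**What the plan says.** The order of events is set in the section on randomisation, blinding and allocation concealment. Eligibility comes first: "Participants who meet the inclusion and exclusion criteria will be randomized into intervention and control groups in a 1:1 ratio". Disclosure follows and differs by arm. "Participants in the intervention group will be informed about the intervention procedure and follow-up plan", whereas controls hear only about follow-up. Then: "If participants agree to their assigned plan, they will sign the informed consent and undergo further baseline assessment".

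The Outcome measures section counts the occasions: "Data will be collected at three different times: post-randomization baseline, 6-month, and 12-month timepoints". Screening is not among them.

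Table 1, captioned "Overview of outcomes and assessment time points", has four time columns: Screening, Baseline, 6 months and 12 months. Frailty, IC, physical functions, body composition and lifestyle factors are ticked in all four. The epigenetic clocks and the other blood-based measures are not ticked at Screening.

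Both secondary outcomes are defined as changes, in frailty score and in IC Z-score. On blinding, the Outcome measures section says: "Data collectors and data entry personnel neither participate in the intervention nor are aware of the participants’ group assignments". The Discussion says of unblinded participants and staff: "We do not consider this to be a significant issue as we will employ blinding for outcome assessors".

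**The concern.** Text and table disagree on how many times these outcomes are measured, and the disagreement bears on the analysis. The occasion missing from the text is the only one that falls before an arm exists. Read as written, the plan takes as baseline a value obtained after the participant knows the arm, although it schedules one without that exposure.

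Several components rest on the participant's own report: GDS-15, self-rated vision and hearing, and fatigue and physical activity in the Fried score. Grip, gait speed and the SPPB depend on effort. A blinded assessor still records whatever a participant who knows the arm reports or is willing to exert. That participants know their arm at baseline is plain from the instruction: "Participants are instructed not to disclose their group assignment to anyone during baseline and follow-up assessments".

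If disclosure moves the baseline differently in the two arms, the difference enters a change score in full and an ANCOVA estimate in part. It could imitate an intervention effect or mask one.

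**Working it through.** **Step 1: sequence.** Eligibility, randomisation, disclosure of the assigned plan, agreement and consent, baseline. The Screening column therefore precedes the arm, and the Baseline column follows knowledge and acceptance of it.

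**Step 2: the plan's own figure.** Only the 74 evaluable participants per arm are needed here. With 20% dropout and 75% adherence, 74/(0.80 × 0.75) = 123.3, rounded up to 124 per arm and 248 in total, as the sample size section states. The 74 itself cannot be rebuilt because no SD is given. At two-sided 0.05 and 90% power it corresponds to a standardised difference of (1.960 + 1.282) × √(2/74) = 0.533. That section sets the 74 for epigenetic age acceleration and frailty, so for IC the 0.533 is only a yardstick.

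**Step 3: illustration for IC.** These inputs are assumptions, not taken from the documents: disclosure shifts the two self-report domains (psychological and sensory) by 0.2 SD between arms, the inter-domain correlation is 0.15, and follow-up is untouched.
- Shift in the five-domain mean: 2 × 0.2/5 = 0.08.
- SD of the composite: √((1 + 4 × 0.15)/5) = 0.566.
- Standardised shift: 0.08/0.566 = 0.14. For shifts of 0.1 and 0.3 SD: 0.04/0.566 = 0.07 and 0.12/0.566 = 0.21.
- Against the yardstick: 0.14/0.533 = 0.27.
- ANCOVA with a baseline slope of 0.5 to 0.7 carries 0.14 × 0.5 = 0.07 to 0.14 × 0.7 = 0.10.

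The 0.14 is in units of the cross-sectional SD. The change-score SD is √(2(1 − ρ)) times as large, where ρ is the baseline-to-follow-up correlation, so the units coincide only at ρ = 0.5. No comparable figure can be given for frailty, because the documents supply no SD or item-level data.

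**Step 4: effect on the test.** Suppose no true effect, 74 per arm, and a baseline shift of b (in cross-sectional SD) that leaves follow-up untouched. The bias is b with SD √(2(1 − ρ)) for change, and ρb with SD √(1 − ρ²) for ANCOVA. The false-positive rate is Φ(δ − 1.96) + Φ(−δ − 1.96), with δ = bias/(SD × √(2/74)).

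| b | Change, ρ = 0.5 to 0.8 | ANCOVA, ρ = 0.5 to 0.8 |
|---|---|---|
| 0 | 5% | 5% |
| 0.1 | 9% to 16% | 6% to 13% |
| 0.2 | 23% to 49% | 11% to 37% |

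Adjusting for the exposed baseline reduces the bias without removing it.

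**Step 5: if the shift persists.** Participants also know their arm at 6 and 12 months. With baseline slope s, the absolute bias is:

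| Analysis | Shift at baseline only | Same shift at follow-up |
|---|---|---|
| Change from post-randomisation baseline | b | 0 |
| ANCOVA on post-randomisation baseline | s × b | (1 − s) × b |
| Change from, or ANCOVA on, Screening value | 0 | b |

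Neither baseline is better under both assumptions.

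**The case against.** The strongest objection is Step 5. A reporting shift that lasts to follow-up cancels in change from the post-randomisation baseline but stays whole if Screening is the baseline. This stands. It is the reason to keep both analyses, and it rules out claiming that the Screening value removes all reporting bias.

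A reader might infer that the baseline actually carries disclosure bias. The documents do not support that. They report no shift, direction or arm difference, and an equal shift in both arms would bias nothing. They do show that the arms are told different things, so equality cannot be presumed.

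A reader might also infer that the Screening values are collected and then discarded. No section says how they are used, and the further baseline assessment mentioned after consent could mean only the items not yet done. The double ticks in Table 1 point the other way, so this is an ambiguity to settle.

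Three practical objections carry some weight.
- The Intrinsic capacity section defines five domains, but the IC row of Table 1 names four and omits the sensory one. That omission covers every time point, so it is not peculiar to Screening, but sensory data at Screening need confirming.
- Centre physicians carry out the screening, while trained collectors gather outcomes, so raters might differ.
- Consent is signed after randomisation. The Study design section calls this further consent, which suggests an earlier one, but use of screening data should be covered explicitly.

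MMSE is also an eligibility measure (scores of 20 or below are excluded), which truncates its screening values. The truncation occurs before randomisation and affects both arms equally.

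**Conclusion.** The point holds as an inconsistency and an exposure. The text names three collection times and a post-randomisation baseline; Table 1 shows four and includes a measurement before the arm exists. The named baseline of both secondary outcomes is open to disclosure bias in self-reported and effort-dependent items, and assessor blinding does not answer that.

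The size of any bias cannot be derived from the documents. The range of 0.07 to 0.21 SD for IC rests on assumed shifts of 0.1 to 0.3 SD in two domains, an assumed inter-domain correlation of 0.15, and no carry-over to follow-up. At zero shift, or an equal shift in both arms, there is no bias. The blood-based outcomes, including the primary ones, have no Screening value and lie outside this point. So does selection through consent given after the arm is known, which a change of baseline value would not address.

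**What to change.** - Make the Outcome measures section and Table 1 agree on the time points.
- For every outcome ticked at Screening (frailty score, IC Z-score, physical functions, body composition, lifestyle factors), define the pre-randomisation Screening value as the analysis baseline. Use it for change and as the ANCOVA covariate.
- Repeat these analyses with the post-randomisation baseline as a prespecified sensitivity analysis. Materially different results would indicate that the conclusion depends on the choice of baseline.
- Confirm that vision and hearing are asked at Screening, and add the sensory domain to the IC row of Table 1.
- Confirm that the screening measures are taken by the same trained collectors and that consent covers their use.
- Keep the post-randomisation baseline for the blood-based outcomes.

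If Screening is carried out as Table 1 shows, no extra visit is needed; the cost is mainly wording plus the confirmations above, and a consent change if screening data are not yet covered. The downsides are a longer gap between baseline and the start of the intervention, possible rater differences at Screening, and MMSE values truncated by the entry cut-off equally in both arms.

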**Figure 2. F0002:**
[figure not shown]
Flow chart of multidomain intervention.

The primary outcomes are the change in epigenetic age acceleration and pace of aging. We will apply eight representative aging clocks in our primary outcomes: Horvath, Hannum, GrimAge, PhenoAge, DunedinPACE, GrimAge version 2, PC-PhenoAge, and PC-GrimAge. Epigenetic age acceleration is defined as the residuals of the linear regression of DNA methylation age on chronological age, which can be calculated by seven clocks (Horvath, Hannum, GrimAge, PhenoAge, GrimAge version 2, PC-PhenoAge, and PC-GrimAge). The rate of aging represented by DunedinPACE is also the primary outcome we are concerned about.

The secondary outcomes are the changes in frailty score and IC Z-score. Other outcomes include physical functions, body composition, aging biomarkers, inflammatory markers, haematology and biochemistry parameters, and lifestyle factors (Table 1).

**Table 1. t0001:** Overview of outcomes and assessment time points.

Outcomes	Outcome measures	Screening	Baseline	6 months	12 months
Primary outcomes					
Epigenetic age acceleration and pace of aging	Horvath, Hannum, GrimAge, PhenoAge, DunedinPACE, GrimAge version 2, PC-PhenoAge, and PC-GrimAge		√	√	√
Secondary outcomes					
Frailty	Fried phenotype	√	√	√	√
Intrinsic capacity	IC Z-score: cognition: MMSE; locomotion: SPPB; vitality: MNA; psychology: GDS-15	√	√	√	√
Other outcomes					
Physical functions	Handgrip strength	√	√	√	√
	Gait speed: 4-m walk test	√	√	√	√
	Timed up-and-go test	√	√	√	√
	Five-times sit-to-stand test	√	√	√	√
Body composition	BMI, waist-to-hip ratio, skeletal muscle mass, skeletal muscle index, body fat percentage, visceral fat area, phase angle	√	√	√	√
Aging biomarkers	Telomere length		√	√	√
	Mitochondrial DNA copy number		√	√	√
Inflammatory markers	hsCRP, homocysteine		√	√	√
	IL-1β, IL-2, IL-4, IL-6, IL-8, IL-10, IL-13, IFN-γ, TNF-α, MCP-1, Eotaxin, CXCL9, CXCL10, CX3CL1, sTNF-R1, sTNF-R2, G-CSF、GM-CSF, VEGF, RANTES, TRAIL		√	√	√
Haematology and biochemistry parameters	Hemoglobin, platelets, neutrophils, hematocrit, white blood cell count; blood urea nitrogen, creatinine, uric acid, glucose, albumin, total bilirubin, alkaline phosphatase, alanine transaminase (ALT), aspartate transaminase (AST), lipid profile		√	√	√
Lifestyle factors	Dietary diversity	√	√	√	√
	Physical activity and sedentary time	√	√	√	√
	Health literacy	√	√	√	√

IC: intrinsic capacity; MMSE: Mini-Mental State Examination; SPPB: Short Physical Performance Battery; MNA: Mini Nutritional Assessment; GDS-15: Geriatric Depression Scale-15; BMI: body mass index; hsCRP: high-sensitivity C-reactive protein. IL-1β: Interleukin-1 beta; IL-2: Interleukin-2; IL-4: Interleukin-4; IL-6: Interleukin-6; IL-8: Interleukin-8; IL-10: Interleukin-10; IL-13: Interleukin-13; IFN-γ: Interferon-gamma; TNF-α: Tumor Necrosis Factor-alpha; MCP-1: Monocyte Chemoattractant Protein-1; CXCL9: C-X-C Motif Chemokine Ligand 9; CXCL10: C-X-C Motif Chemokine Ligand 10; CX3CL1: C-X3-C Motif Chemokine Ligand 1; sTNF-R1: Soluble Tumor Necrosis Factor Receptor 1; sTNF-R2: Soluble Tumor Necrosis Factor Receptor 2; G-CSF: Granulocyte Colony-Stimulating Factor; GM-CSF: Granulocyte-Macrophage Colony-Stimulating Factor; VEGF: Vascular Endothelial Growth Factor; RANTES: Regulated on Activation, Normal T Cell Expressed and Secreted; TRAIL: Tumor Necrosis Factor-Related Apoptosis-Inducing Ligand.

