The third-generation epigenetic clocks, such as DunedinPACE [42], GrimAge version 2 [43], PC-PhenoAge and PC-GrimAge [44], are characterized by their integration of multi-dimensional data, optimization of algorithms and models, and ability to comprehensively assess individual health status, disease risk, and the effects of aging interventions. DunedinPACE [42] is developed based on longitudinal changes in multi-system biomarkers, reflecting the pace of aging, with its unit expressed as ‘years/calendar year’. GrimAge version 2 [43] expandes upon the original GrimAge by incorporating additional DNA methylation (DNAm)-based surrogates for clinically relevant plasma proteins (DNAm logCRP and DNAm logA1C). PC-PhenoAge and PC-GrimAge [44] are epigenetic clocks optimized based on principal component analysis (PCA). They utilize principal components derived from the CpG sites of the foundational PhenoAge and GrimAge clocks, offering high reliability and potential applications in personalized medicine, longitudinal tracking, *in vitro* studies, and clinical trials of aging interventions.

We have introduced a novel variable, ‘Mean EpiAge’ [45], which is calculated as the average methylation age derived from seven established epigenetic clocks: Horvath, Hannum, GrimAge, PhenoAge, GrimAge version 2, PC-PhenoAge, and PC-GrimAge. Notably, DunedinPACE is excluded from the computation of Mean EpiAge because it specifically quantifies the pace of aging rather than providing a methylation age estimate. The development of Mean EpiAge aims to reconcile discrepancies between DNA methylation age and chronological age that arise from the use of different epigenetic clocks, thereby offering a more comprehensive measure of biological aging. We will focus on the results of each epigenetic clock because they enable us to conduct comparisons with studies that utilize the same clocks. Similarly, we pay attention to the Mean EpiAge, as it represents an overall and comprehensive aging outcome.

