### Statistical analysis

This study will follow the intention-to-treat principle for statistical analysis, including participants who complete baseline assessments and at least one follow-up assessment in the final analysis. Normally distributed continuous variables with a normal distribution will be presented as mean ± standard deviation, while non-normally distributed continuous variables will be presented as median (interquartile range). Categorical variables will be presented as frequencies and percentages (%). For the baseline data comparison between the control group and the intervention group, independent samples t-test will be used for normally distributed continuous variables, Mann-Whitney U test for non-normally distributed continuous variables, and chi-square test or Fisher’s exact test for categorical variables. Repeated measures analysis of variance will be used to analyze the changes in primary and secondary outcomes within the intervention and control groups, with multiple comparisons corrected using Bonferroni adjustment. Repeated measures analysis of covariance will be employed to compare the differences in primary and secondary outcome measures between the intervention and control groups at different follow-up times. The statistical analysis will be conducted using R language version 4.0.3 and SPSS 25.0 statistical software. Hypothesis testing will be conducted using two-tailed tests with a significance level of α = 0.05, where *p* < 0.05 is considered statistically significant.

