Currently, some scholars have conducted intervention studies targeting biological age. Most of these studies have implemented dietary and exercise interventions in obese populations. For example, a one-year intervention combining diet and exercise in 107 obese older adults found that both the diet group and the diet-plus-exercise group showed a reduction in Klemera Doubal Method (KDM) biological age at the 6-month and 12-month follow-up assessments. Specifically, at 6 months, the diet group showed a reduction of 1.4 years, while the diet-plus-exercise group showed a reduction of 1.7 years. At 12 months, the diet group showed a reduction of 2.4 years, and the diet-plus-exercise group showed a reduction of 2.2 years [61]. In the Israeli CENTRAL study, 120 obese individuals underwent an 18-month weight-loss intervention combining diet and exercise, which resulted in a 7.1-month delay in methylation age compared to the expected aging in the older male subgroup [62]. Similarly, a U.S. study involving 16 obese older adults implemented a 3-month intervention consisting of dietary counseling and a combination of aerobic and resistance exercise. However, this study found no statistically significant reduction in three types of methylation age (Horvath, Hannum, and PhenoAge clocks) after the intervention [63]. In the widely recognized CALERIE study on caloric restriction, 128 normal-weight or mildly overweight participants underwent a 25% caloric restriction for 2 years. The pace of aging, as measured by DunedinPACE, slowed by 2%∼3% in the caloric restriction group (equivalent to a 10%∼15% reduction in mortality risk), but no significant changes were detected using the other two aging clocks (PC-PhenoAge and PC-GrimAge) [64].

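### Eight clocks are co-equal primary outcomes, but the between-arm tests are unadjusted at 0.05 and Bonferroni is attached only to the within-group comparisons

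*Protocol article*

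**What the plan says.** - **Primary outcomes.** The Outcome measures section (text below Figure 2) states "We will apply eight representative aging clocks in our primary outcomes". Seven clocks supply an age-acceleration residual. Of the eighth it adds "The rate of aging represented by DunedinPACE is also the primary outcome we are concerned about". Table 1 puts all eight in the primary row, measured at baseline, 6 and 12 months. No clock leads.
- **How the clocks are read.** The section on epigenetic age acceleration and pace of aging says "We will focus on the results of each epigenetic clock because they enable us to conduct comparisons with studies" that use the same clocks. It also defines Mean EpiAge, an average over seven clocks, and says "we pay attention to the Mean EpiAge, as it represents an overall and comprehensive aging outcome". Table 1 does not list Mean EpiAge.
- **Analysis.** The Statistical analysis section uses repeated measures ANOVA for changes "within the intervention and control groups, with multiple comparisons corrected using Bonferroni adjustment". The next sentence uses repeated measures ANCOVA to compare primary and secondary outcomes "between the intervention and control groups at different follow-up times" and mentions no correction. The general rule is two-tailed testing at 0.05.
- **Sample size.** The Calculation of sample size section gives 74 per group for 90% power at p < 0.05 in epigenetic age acceleration and frailty at 12 months. It names no clock and does not split alpha.

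**The concern.** Change within an arm does not estimate the effect of the intervention; only the contrast between arms does. The plan corrects the former and leaves the latter at 0.05 for each of eight primary measures. In a within-group repeated measures ANOVA, the Bonferroni step most naturally covers the pairwise time contrasts, so it does not obviously deal with the number of clocks even there.

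At stake is the error rate of the trial's main claim. With eight primary measures each tested at 0.05, an ineffective intervention yields at least one significant primary result well over 5% of the time. Disagreement between clocks is also likely. The Discussion describes a two-year caloric-restriction trial in which DunedinPACE slowed by 2% to 3% while PC-PhenoAge and PC-GrimAge showed no significant change. All three are primary here, and the protocol does not say how such a pattern would be read.

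**Working it through.** **1. The plan's own figure.** Inputs from the sample size section: 74 evaluable per group, 20% dropout, 75% adherence. 74 / (0.80 × 0.75) = 123.3, rounded up to 124 per group, 248 in total. This reproduces. The 74 itself cannot be checked, because no standard deviation is given.

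**2. False-positive chance at 12 months only.** Eight between-arm tests, two-sided 0.05, no true effect on any clock.

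- Independent tests: 1 − 0.95^8 = 0.337. Counting only results favouring the intervention (0.025 per test): 1 − 0.975^8 = 0.183.
- Correlated tests: simulation of eight equally correlated normal test statistics, 200,000 draws. The protocol gives no correlations, so these are assumed.

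| Between-clock correlation (assumed) | At least one two-sided p < 0.05 | At least one in the slower-aging direction |
|---|---|---|
| 0 (upper bound) | 34% | 18% |
| 0.3 | 30% | 15% |
| 0.5 | 25% | 13% |
| 0.7 | 19% | 10% |
| 0.8 | 16% | 8% |
| 0.9 | 12% | 6% |

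The benchmarks are 5% for the middle column and 2.5% for the right-hand one. A pattern closer to the actual clocks (three GrimAge versions at 0.9, two PhenoAge versions at 0.8, all other pairs 0.2 to 0.4, also assumed) gives 24% to 27% two-sided and 12% to 13% directional.

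**3. If the 6-month contrasts also count.** Sixteen independent tests give 1 − 0.95^16 = 0.560. With a between-visit correlation of 0.5 (assumed), the two-sided figure is 48%, 41%, 32%, 27% and 21% for between-clock correlations of 0.3, 0.5, 0.7, 0.8 and 0.9.

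**4. Power if all eight stay primary.** The effect must be back-solved from 74 per arm, 90% power and two-sided 0.05:

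- Standardized effect = (1.960 + 1.282) × √(2/74) = 0.533. With the 0.66-year reference effect this implies an SD of 0.66 / 0.533 = 1.24 years.
- Bonferroni alpha = 0.05 / 8 = 0.00625, critical value 2.734.
- Power at 74 per arm = Φ(0.533 / √(2/74) − 2.734) = Φ(3.242 − 2.734) = Φ(0.508) ≈ 0.69.
- For 90% power per clock: 2 × (2.734 + 1.282)² / 0.533² ≈ 113.6, so 114 evaluable per arm instead of 74.

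**The case against.** Several points on the other side are sound.

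- **The clocks overlap.** GrimAge, GrimAge version 2 and PC-GrimAge share a basis, as do PhenoAge and PC-PhenoAge. The independence figures (34%, and 56% for sixteen tests) are therefore upper bounds. The correlated range is the one to use.
- **The claim is directional.** A conclusion that aging was delayed counts only results in one direction. The two-sided rates overstate that error, and the right benchmark is 2.5%. At correlation 0.9 the directional rate is only about 6%.
- **The visit is indicated.** The sample size section powers 12 months, and a repeated measures ANCOVA can give one group test per clock. A reader might infer sixteen separate primary tests, but the text does not compel that reading.
- **Mean EpiAge is not primary.** A reader might take it for a ninth primary test because it is called an overall outcome. It is neither labelled primary nor listed in Table 1. Adding it to the correlated clocks changes the rates by less than one percentage point.
- **No success rule is written.** A reader might infer that any one significant clock will be declared a success. The protocol does not say so, and the reason it gives for reporting each clock is comparison with other studies.
- **An analysis plan not shown may add a multiplicity rule.** It may. But the protocol itself fixes the eight primaries, the place of the correction and the threshold. A plan that adjusted the between-arm tests would depart from that text, and the stated power would need rechecking.

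These points reduce the size of the problem without removing it: inflation remains at every correlation examined, for one visit and one direction.

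**Conclusion.** The point holds in this form: eight co-equal primary clocks, between-arm tests unadjusted at two-sided 0.05, and the only stated correction placed on within-group comparisons.

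On the reading kindest to the plan, 12 months only, the error rate is about 2.4 to 6 times nominal: 12% to 30% against 5% two-sided, or 6% to 15% against 2.5% in the favourable direction. It is higher if the 6-month contrasts count. The range rests on assumed between-clock correlations of 0.9 to 0.3.

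The conclusion does not depend on Mean EpiAge, on counting both visits, or on supposing that one positive clock will be called success. The power figure of 69% rests on an effect of about 0.53 SD that is back-solved, not stated. It cannot be carried over to DunedinPACE without support, because the reference effect is in years of age acceleration and DunedinPACE is in years per calendar year.

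**What to change.** Before any between-arm methylation result is seen:

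1. State that the between-arm difference at 12 months is the confirmatory comparison.
2. Choose one of two routes; the choice is the sponsor's.
   - Keep all eight clocks primary and apply Holm or max-T across the eight between-arm tests at overall two-sided 0.05.
   - Name one primary measure and report the other clocks as supportive estimates with confidence intervals.
3. Label the 6-month contrasts supportive and the within-group tests descriptive.
4. State whether Mean EpiAge is supportive or has another role.

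**Cost.** The first route leaves the outcome list intact, but the power must be restated: about 69% per clock under Bonferroni at 74 per arm, which Holm can only match or improve, with 114 evaluable per arm needed for 90%. The second route keeps the stated alpha and power, provided the effect assumed for the chosen measure is justified. It changes the listed primary outcomes of a registered, ethics-approved trial, so it needs a dated amendment and a registry update. Neither route requires new data collection.
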